#### Interrater variability

Bland-Altman analysis will be performed on log-transformed volumes to obtain ratio-based limits of agreement. Reliability will be calculated using the intraclass correlation coefficient (ICC; two-way random effects model, absolute agreement, single measures) and Lin’s concordance correlation coefficient (CCC), both reported with 95% confidence intervals. ICC values will be interpreted according to established procedures [30]: <0.50 poor, 0.50–0.75 moderate, 0.75–0.90 good, and > 0.90 excellent.

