### Primary outcome

The primary outcome is the change in WMH volume based on brain MRI measurements.

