#### Sample size

We aim to include 60 patients in the three study groups, resulting in a maximum total number of 180 patients. We expect a drop-out proportion of 25%, relating to difficulties of mobility and morbidity for adherence in follow-up visits of patients with territorial brain ischemia in particular and considering the rural area surrounding the region of Ulm, Baden-Württemberg, Germany. The calculation of sample size is not based on a confirmatory study aim, but is exploratory and mirrors our experiences made in the pilot study of the recruitment that can be expected and delivered in our clinical setting in Ulm.

As an illustration of sensitivity: in a pilot subset (unpublished data) with paired manual WMH volumetry (17 patients), the mean 12-month WMH volume change was 5.30 mL (SD 6.03; standardized within-subject effect d_z ≈ 0.88). A within-group comparison detects a change of this magnitude at ~ 80% power (two-sided α = 0.05) in ~ 10 patients per group. With 60 patients per group (≈ 45 completing follow-up after the anticipated 25% drop-out), the planned cohort is sensitive to within-subject WMH changes as small as d_z ≈ 0.36 (at 60 per group) to 0.42 (at 45 per group), i.e. ≈ 2.2–2.5 mL, well below the 5.30 mL observed in the pilot data, and, for exploratory between-group comparisons, to standardized differences of d ≈ 0.51 (at 60 per group) to 0.59 (at 45 per group), a ≈ 3.1–3.6 mL difference in WMH change between groups.

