Features of CSVD are determined according to STandards for ReportIng Vascular changes on nEuroimaging (STRIVE) criteria [2]. This will be conducted by trained (neuro-)radiologists and vascular neurologists considering the above-mentioned sequences (especially FLAIR, T1-weighted MPRAGE, DWI, and SWI or T2*). Interrater reliability will be calculated for the determined volume of CSVD, the presence or absence of cerebral microbleeds, lacunes, and perivascular spaces using a set of randomly selected patients.

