To account for scanner differences between acquisitions, WMH segmentation will be performed using a FLAIR-only automated in-house pipeline based on the half-Gaussian mixture model described by Igwe et al. [25], which models log-transformed above-mode FLAIR intensities as a two-component mixture: a half-Gaussian for normal-appearing white matter and a full Gaussian for WMH, with all five parameters estimated via expectation-maximization. The original method was validated on a single scanner and timepoint; we extend it to longitudinal cross-scanner comparison by fitting the HGMM independently per timepoint on a shared white matter territory (intersection of both timepoints’ white matter labels), with a two-pass refinement that excludes candidate WMH from the fit pool to tighten the normal-appearing white matter model. Longitudinal change is estimated through paired voxel-wise contrast at the TP1 lesion boundary, corrected for scanner offset (estimated from stable white matter) and blur mismatch, rather than by subtracting two independent segmentations. Anatomical false positives are removed through automated exclusion. Acute DWI lesions identified on the baseline MRI were registered to FLAIR space andexcluded from the WMH volume calculations at baseline, 6-month, and 12-month follow-up. This procedure ensured that longitudinal WMH measurements represented chronic white matter disease burden, independent of the baseline acute infarct.

In the pilot cohort, baseline and follow-up FLAIR were acquired on different scanners and protocols, so standard endpoint WMH segmentation could not reliably separate true lesion change from scanner-induced contrast shifts. We therefore used a scanner-aware longitudinal pipeline designed to identify the FLAIR change as biological progression rather than scanner change artifacts. Since the prospective cohort is acquired on a stable, harmonized protocol, Deep WMH and Multi-site Auto-segmentation and Registration of Subcortical White Matter Hyperintensities (MARS)-WMH-derived segmentation will additionally be evaluated, with agreement to the manual reference quantified by Dice similarity coefficient and ICC.

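### Rater and tool agreement is defined on WMH volume, but the primary outcome is within-patient change, so even an excellent volume ICC would leave the error in change unknown.

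*Protocol article*

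**What the plan says.** The Primary outcome section reads: "The primary outcome is the change in WMH volume based on brain MRI measurements". The Sample size section expresses that change in mL over 12 months.

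Agreement is described in three places:

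- **Magnetic resonance imaging:** "Interrater reliability will be calculated for the determined volume of CSVD", along with some categorical markers, in a random set of patients.
- **Interrater variability:** "Bland-Altman analysis will be performed on log-transformed volumes to obtain ratio-based limits of agreement". Reliability uses the "intraclass correlation coefficient (ICC; two-way random effects model, absolute agreement, single measures") and Lin's concordance coefficient. The ICC is read on the bands "<0.50 poor, 0.50–0.75 moderate, 0.75–0.90 good, and > 0.90 excellent".
- **Postprocessing:** two further automated segmentation methods will be evaluated, "with agreement to the manual reference quantified by Dice similarity coefficient and ICC". The same section says that the in-house pipeline obtains longitudinal change from a paired voxel-wise contrast at the baseline lesion boundary, corrected for scanner offset and blur, and not as the difference of two separate segmentations.

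None of these places names a visit, and none applies an agreement statistic to the change.

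**The concern.** An ICC compares measurement error with the spread between patients. Eligibility runs from Fazekas grade 1 to 3, so the spread of WMH volume may be wide, and a wide spread raises a volume ICC whatever the error in a patient's own change. The Bland-Altman analysis does not close the gap. It is done on log volumes, and the log of a change that is zero or negative does not exist. The Introduction itself notes that CSVD may partly regress.

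The study's first objective is to find blood biomarkers that track progression, and the Statistical methods section relies on individual slopes and correlations. Error in the measured change attenuates those correlations. An excellent volume ICC would not tell the reader how large that attenuation is, nor which segmentation tool follows change best.

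**Working it through.** **1. The plan's own figures.** Inputs from Sample size: "the mean 12-month WMH volume change was 5.30 mL (SD 6.03; standardized within-subject effect d_z ≈ 0.88"), and "at ~ 80% power (two-sided α = 0.05) in ~ 10 patients per group". With z-values 1.96 + 0.842 = 2.802:

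- Pilot effect: 5.30/6.03 = 0.88; n = (2.802/0.88)² = 10.1.
- Within group: 2.802/√60 = 0.36 and 2.802/√45 = 0.42. Times 6.03, these are 2.2 and 2.5 mL.
- Between groups: 2.802·√(2/60) = 0.51 and 2.802·√(2/45) = 0.59. Times 6.03, these are 3.1 and 3.6 mL.

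All stated values reproduce under the normal approximation.

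**2. What a volume ICC implies for change.** Suppose change is the difference of two volumes, S is the between-patient SD of volume, and ρ is the correlation of measurement errors across visits. Then

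error SD of change = S·√(2(1 − ICC)(1 − ρ)).

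The article gives neither S nor ρ, so both are assumptions. With ρ = 0:

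| Volume ICC | S = 5 mL | S = 10 mL | S = 15 mL |
|---|---|---|---|
| 0.90 | 2.2 mL | 4.5 mL | 6.7 mL (not compatible) |
| 0.95 | 1.6 mL | 3.2 mL | 4.7 mL |
| 0.99 | 0.7 mL | 1.4 mL | 2.1 mL |

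The 6.7 mL entry exceeds the pilot's total SD of change of 6.03 mL. Independent error is only one part of that total, so this combination would need a higher ICC or correlated errors. With ρ = 0.5 and S = 10 mL, the ICC 0.90 figure falls from 4.5 to 3.2 mL.

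**3. Reliability of change.** Reliability = 1 − (error SD/6.03)², and a correlation with change is multiplied by its square root. For S = 10 mL and ρ = 0:

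- ICC 0.90: 1 − 20/36.36 = 0.45; √0.45 = 0.67.
- ICC 0.95: 1 − 10/36.36 = 0.72; √0.72 = 0.85.
- ICC 0.99: 1 − 2/36.36 = 0.94; √0.94 = 0.97.

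A simulation of two raters reading two visits, with the observed SD of change held at 6.03 mL, agrees. A volume SD of 10 mL with a volume ICC of 0.92 gives an ICC of change of 0.56. A volume SD of 15 mL with a volume ICC of 0.95 gives 0.38. On the plan's own bands these are excellent for volume, but moderate and poor for change.

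**4. The paired voxel-wise estimator.** The formula in step 2 does not apply to the in-house pipeline, because that pipeline does not subtract two volumes. Neither a volume ICC nor Dice examines the quantity it produces, so its error in change cannot be derived from the planned statistics.

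**The case against.** Several counter-arguments stand.

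- **Detectable effects.** A reader might infer that a per-patient error of 3 to 4 mL undermines the stated sensitivity of 2.2–2.5 mL within groups and 3.1–3.6 mL between groups. It does not. Those are effects on group means, and the SD of 6.03 mL comes from paired manual volumetry, so it already contains random measurement error. The standard error of a group mean at 45 patients is 6.03/√45 = 0.90 mL. Random error in the outcome also widens the interval around a group difference without shrinking the difference.
- **Larger error figures.** A reader might assume a volume SD of 20 mL, which gives 8.9 mL at ICC 0.90 and 6.3 mL at ICC 0.95. Both exceed 6.03 mL and cannot be used.
- **Spread and Bland-Altman.** Ratio limits are not inflated by between-patient spread, so the ICC would not stand alone. Even so, turning a ratio error in volume into an error in change needs the patient's volume and the error correlation across visits.
- **Rater offset.** An absolute-agreement ICC counts a constant offset between raters. That offset cancels in change if one rater reads both scans, so the formula can overstate the error.
- **Tool selection.** A reader might infer that ICC or Dice decides which tool is used. No section says so; the bands are descriptive labels and the tools are only to be evaluated.
- **Level of detail.** Which visits enter the reliability subset is detail that an article may leave to the full protocol, and the study is exploratory. However, the article does fix the statistic, its form, its scale and its bands, and all of them concern volume.

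**Conclusion.** The point holds as a mismatch between what the agreement analysis measures and what the study analyses. That agreement is on volume rather than change is read from the wording and the log scale; the article names no visit.

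The size is conditional. Under simple subtraction, independent errors and an assumed volume SD of 10 mL, a volume ICC of 0.90 to 0.95 would go with a reliability of change of about 0.45 to 0.72. For a volume SD of 5 mL, the error SD is only 0.7 to 2.2 mL over ICC 0.99 to 0.90, and the effect is small. The pilot SD of 6.03 mL rests on 17 patients scanned on differing systems, so these figures are illustrative. Only an agreement analysis of the change can show which case applies.

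At risk are the reading of individual change, the strength of correlations between biomarkers and WMH change, and the comparison of segmentation tools. The sample-size statements are unaffected. This is a worthwhile improvement and does not invalidate the design.

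**What to change.** In the planned random reliability subset, drawn from patients who have both scans, have the existing raters and each automated tool measure the baseline and the 12-month scan. For the 12-month change, report:

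- the ICC with its 95% confidence interval;
- Bland-Altman limits in mL;
- the smallest detectable change (1.96 × the error SD of change), set beside the pilot SD of change of 6.03 mL.

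For the in-house pipeline, use its own paired estimate of change. Compare the tools on agreement in change as well as on Dice and volume ICC. Keep the log-volume limits, ICC and concordance coefficient as secondary description.

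The cost is some extra reading time for existing raters on scans already scheduled, and a few lines of R. The reported reliability may look less favourable than a volume ICC alone.

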## Data Availability

No datasets were generated or analysed during the current study.

## Abbreviations

Aβ: Beta-amyloid
ADC: Apparent Diffusion Coefficient
ADL: Activities of Daily Living
ASL: Arterial Spin Labeling
BSI: German Federal Office for Information Security
CCC: Concordance Correlation Coefficient
CSVD: Cerebral Small Vessel Disease
DECT: Digital Enhanced Cordless Telecommunications
DICOM: Digital Imaging and Communications in Medicine
DTI: Diffusion-Tensor Imaging
DWI: Diffusion-Weighted Imaging
EQ-5D: EuroQol 5 Dimension
eCRF: Electronic case report form
FA: Fractional anisotrophy
FLAIR: Fluid Attenuated Inversion Recovery
GCP: Good Clinical Practice
GDS: Geriatric Depression Scale
GFAP: Glial Fibrillary Acidic Protein
GSP: Good Scientific Practice
HbA1c: Glycated Hemoglobin
HDL: High-Density Lipoprotein
IADL: Instrumental Activities of Daily Living
ICC: Intraclass Correlation Coefficient
ICF: Informed Consent Form
ISCED: International Standard Classification of Education
ISCO: International Standard Classification of Occupations
KRITIS: Critical Infrastructures
LDL: Low- Density Lipoprotein
MARS: Multi-site Auto-segmentation and Registration of Subcortical White Matter Hyperintensities
MPRAGE: Magnetization-Prepared Rapid Gradient Echo
MoCA: Montreal Cognitive Assessment
MRI: Magnetic Resonance Imaging
mRS: Modified Rankin Scale
NfL: Neurofilament Light Chain
NIHSS: National Institutes of Health Stroke Scale
NPA: Neuropsychologic assessment
NVDU: Neurovascular Doppler ultrasound
PSMD: Peak width of skeletonized mean diffusivity
pTau217: Phosphorylated Tau 217
QoL: Quality of Life
RBANS: Repeatable Battery for the Assessment of Neuropsychological Status
STRIVE: STandards for ReportIng Vascular changes on nEuroimaging
SWI: Susceptibility-Weighted Imaging
TAP: Test of Attentional Performance
TOF-MRA: Time-of-Flight MR Angiography
VCAM-1: Vascular Cell Adhesion Molecule-1
VEGF: Vascular endothelial growth factor
WAI: Work Ability Index
WMH: White Matter Hyperintensities
